**LIST OF ABBREVIATIONS AND RELEVANT DEFINITIONS**

| **ABR** | **ABR form (General Assessment and Registration form) is the application form that is required for submission to the accredited Ethics Committee (ABR = Algemene Beoordeling en Registratie)** |
| --- | --- |
| **AE** | **Adverse Event** |
| **AR** | **Adverse Reaction** |
| **CA** | **Competent Authority** |
| **CCMO** | **Central Committee on Research Involving Human Subjects** |
| **CV** | **Curriculum Vitae** |
| **DSMB** | **Data Safety Monitoring Board** |
| **EU** | **European Union** |
| **EudraCT** | **European drug regulatory affairs Clinical Trials GCP Good Clinical Practice** |
| **IB** | **Investigator’s Brochure** |
| **IC** | **Informed Consent** |
| **IMP** | **Investigational Medicinal Product** |
| **IMPD** | **Investigational Medicinal Product Dossier** |
| **METC** | **Medical research ethics committee (MREC); in Dutch: medisch ethische toetsing commissie (METC)** |
| **(S)AE** | **Serious Adverse Event** |
| **SPC** | **Summary of Product Characteristics (in Dutch: officiële productinfomatie IB1-tekst)** |
| **Sponsor** | **The sponsor is the party that commissions the organisation or performance of the research, for example a pharmaceutical**  **company, academic hospital, scientific organisation or investigator. A party that provides funding for a study but does not commission it is not regarded as the sponsor, but referred to as a subsidising party.** |
| **SUSAR** | **Suspected Unexpected Serious Adverse Reaction** |
| **Wbp** | **Personal Data Protection Act (in Dutch: Wet Bescherming Persoonsgevens)** |
| **WMO** | **Medical Research Involving Human Subjects Act (Wet Medisch-wetenschappelijk Onderzoek met Mensen** |

**SUMMARY**

**Rationale:** Diabetic nephropathy is a serious complication of diabetes mellitus, which is the leading cause of end-stage renal disease (ESRD) in the Western World. Benfotiamine has been shown to reduce diabetic nephropathy and retinopathy in animal experimental models. We will investigate the effect of benfotiamine supplementation in patients with diabetic nephropathy, and hypothesize that it will slow down the progression to ESRD if it leads to reduction of tubulointerstitial damage and inflammation.

**Objectives**:

-To investigate whether short-term treatment (3 months) with benfotiamine leads to a reduction in urinary excretion of β2-microglobulin and albumin.

-To investigate whether short-term treatment (3 months) with benfotiamine leads to reduction in urinary excretion of markers of renal tubulointerstitial damage and inflammation (Kidney Injury Molecule-1, Monocyte Chemo-attractant Protein-1, Macrophage Inhibiting Factor, Complement factor C3d)

**Study design:** Mono-center, randomized, controlled, double-blind, parallel group clinical trial studying the effect of high dose benfotiamine compared to placebo in 86 patients with diabetic nephropathy. The study consists of 2 phases;

1-Run-in phase (6 weeks): In this phase patients will be instructed on collection of 24h urine samples, it will be checked whether they have urinary albumin excretion consistently in the microalbuminuric range, and they will be instructed on maintenance of stable diet and activity levels prior to the study visits to the outpatient clinic.

2-Treatment phase (12 weeks): According to randomization, benfotiamine is given to one half of the patients and placebo is given to the other half.

**Study population:** ***40–75 year old patients with type 2 diabetes mellitus (T2DM)*** and diabetic nephropathy with microalbuminuria (30-300 mg/24 h urine) and glomerular filtration rate (eGFR, estimated by MDRD formula) > 30 ml/min

**Intervention**
Group A: Benfotiamine (300 mg) 3x 1 film coated tablet daily (900 mg daily dose benfotiamine)
Group B: Placebo 3x 1 film coated tablet daily

The intervention duration is 12 weeks for each group.

**Main study parameters/endpoints:**

Change in urinary excretion of:

• β2-microglobulin

• Albumin

**Nature and extent of the burden and risks associated with participation, benefit and group relatedness:**

-The patients are asked to attend the outpatient clinic for the study 5 times in total. Before each visit the patients are asked to collect a 24h urine sample. They will be asked to refrain from food from the previous evening to take fasting blood samples (5 vials of 7 ml). In addition, a second-morning urine sample will be collected.

- No other physical or physiological discomfort in association with participation is anticipated than the discomfort associated with the collection of the 24h urine samples and the blood sampling. There are no known risks associated with the investigational product other than the rare occurrence of urticaria and pruritus. In case of positive effects on diabetic nephropathy (albuminuria) a program on prophylaxis and treatment of diabetic nephropathy with benfotiamine will be taken into account. Benfotiamine will be investigated to assess its effect on markers of tubulointerstitial damage and inflammation associated with diabetic nephropathy. If it will be demonstrated that benfotiamine causes an improvement in these markers, the drug may become eligible for further large studies on its efficacy in prevention of the development of end-stage renal disease in susceptible diabetic patients. Participation of diabetic nephropathy patients in this study is of great importance, and answering the questions of this clinical trial is not possible without observing and analyzing the parameters at the end of the study.

# INTRODUCTION AND RATIONALE

There is a worldwide increase in prevalence in type 2 diabetes mellitus (1), which is being paralleled by an increasing number of patients reaching dialysis because of diabetic nephropathy (2). Much of the fivefold increase in patients receiving dialysis treatment that occurred over the past two decades is attributable to type 2 diabetes and diabetic nephropathy (3). Diabetes is now the leading cause of end-stage renal disease (ESRD), with more than 40% of all new cases of ESRD occurring in patients with diabetes (3).

The pathophysiology of diabetic nephropathy and progression to ESRD is essentially composed of two components. The first is induction of glomerular endothelial dysfunction by hyperglycaemia, leading to albuminuria (4). The second is tubulo-interstitial inflammation and fibrosis, which is much more the consequence of albuminuria (5,6), although hyperglycaemia may accelerate the process (7). Tight glycaemic control has been shown to reduce the risk for development of albuminuria in patients with diabetes, as shown in several controlled trials in type 1 and type 2 diabetes (8-11). However, once established, glomerular lesions and albuminuria are reversible, but poorly. It has been shown to take at least five years of normalisation of glucose concentrations by pancreas transplantation before glomerular lesions and albuminuria decreased (12). Glycaemic control has, therefore, only limited influence on progression to ESRD once albuminuria is present (2). Currently, reduction of albuminuria with antihypertensive/antiproteinuric treatment, in particular with angiotensin-converting enzyme inhibitors (ACEi) and angiotensin II antagonists (AIIA) is the cornerstone of prevention of progression of overt diabetic nephropathy to ESRD (13-15). Reductions in relative risk for decline in renal function were approximately 50% with ACEi treatment in patients with type 1 diabetes (13). These risk reductions were considerably less – approximately 20% – for the end-point of doubling of serum creatinine or reaching ESRD in type 2 diabetic patients with diabetic nephropathy (14,15).

Thus, there is great need for further adjunctive treatments that can prevent progressive decline in renal function in patients with diabetic nephropathy, in type 2 diabetes in particular. Several studies suggest that in non-diabetic proteinuric diseases, albuminuria and/or proteinuria induce oxidative stress and accumulation of advanced glycation end-products (AGEs) (independent of glucose concentrations) in tubular epithelial cells and the renal interstitium, which elicit proinflammatory and profibrotic responses that contribute to chronic tubulointerstitial damage and loss of renal function (16-21). Hyperglycaemia, which is also known to induce oxidative stress and AGE accumulation, may obviously enhance these detrimental effects of albuminuria/proteinuria (7). The lipid-soluble thiamine derivative benfotiamine, has recently been shown to be able to oppose the induction of oxidative stress and AGE accumulation by hyperglycaemia (22). Optimal thiamine availability is crucial for the maintenance of enzymatic anti-oxidant defence in cells (23,24). Benfotiamine has recently been shown to be able to reduce diabetic nephropathy and retinopathy in animal experimental models (22,25). Thornalley et al have recently found that diabetes induces thiamine deficiency in tissues in humans (26). We therefore hypothesize that benfotiamine supplementation in patients with diabetic nephropathy will ameliorate the effects of both albuminuria/proteinuria and hyperglycaemia on oxidative stress and AGE accumulation in renal tissue, and thereby decrease inflammatory and fibrotic responses, causing slowing down of progression to ESRD as a consequence.

# OBJECTIVES

*Primary Objectives:*

-Does short-term treatment (3 months) with benfotiamine in diabetic nephropathy result in a lowering of urinary excretion of β2-microglobulin and albumin?

*Secondary Objectives:*

-Does short-term treatment (3 months) with benfotiamine result in a lowering of urinary excretion of established and emerging markers of tubulointerstitial damage and inflammation, such as KIM-1, MIF, MCP-1, and C3d in patients with diabetic nephropathy (the expression of MCP-1 in the kidney and the amounts of MCP-1 in urine have, for instance, been shown to be associated with severity of tubulointerstitial disease and to predict the loss of renal function in several types of chronic kidney disease (27-32))?

# STUDY DESIGN

In this mono-center, randomized, controlled, double-blind clinical trial with 2 parallel groups (verum versus placebo) to investigate the effect of high dose benfotiamine on urinary excreation of β2-microglobulin and albumin in patients with diabetic nephropathy. The study medication will be added upon existing treatment for diabetic nephropathy. The study consists of following phases:

***Run-in phase (6 weeks):***

During this phase, patients will be instructed on collection of 24-hour urine sample before each visit to the outpatient clinic. Patient will also be checked whether they have urinary albumin excretion consistently in the microalbuminuric range by doing a 24 hour-urine analysis on two different occasions with 2-6 weeks in between. They will be instructed on maintenance of stable diet and physical activity prior to each visit to the outpatient clinic.

***Treatment phase (12 weeks):***

After the patients are randomly divided into two groups, the treatment is given for both groups for 12 weeks in a double-blind pattern. One group will be given the study medication, and the other will be given the placebo.

During this phase patient are asked to attend the outpatient clinic 2 times:

*-Week 0 (the beginning of the phase)*

*-Week 6*

*-Week 12 (the end of the phase)*

In each visit of these, fasting blood samples (5 vials of 7 ml) are drawn for analysis (blood glucose, HBA1c, and other parameters), second-morning urine sample is collected, and 24-hour urine (of the preceding day) is sent to the laboratory for analysis.

# STUDY POPULATION

## Population

The population of this trial consists of 40-75 year old, male and female patients with type 2 diabetes mellitus.

## Inclusion criteria

• Type 2 diabetes mellitus
• Age: 40-75 years
• Patients are on treatment with angiotensin converting enzyme inhibitors (ACEi) and/or angiotensin II antagonists (AIIA) in an unchanged dose for at least 3 months
• Active diabetic nephropathy as indicated by presence of microalbuminuria (30-300 mg/24 h urine) in at least two samples within 2-6 weeks in advance of inclusion in the trial
• HbA1c < 8.5%, a higher HbA1c  9.5% is acceptable if the treating physician and the patient have accepted that striving for lower values is an unreachable goal (patients with high HbA1c values are the ones that one would expect to be benefit most from treatment with benfotiamine)
• eGFR (estimated by MDRD formula) > 30 ml/min
• Males and postmenopausal females
• Written informed consent

## Exclusion criteria

• Renal impairment by other causes than diabetes
• Stage of the disease more severe than indicated in "Inclusion criteria"
(macroalbuminuria or renal insufficiency)
• Severe hypoglycemia during the last 3 months, needing help from another person
• Severe hepatopathy (liver function enzymes about three times higher than normal)
• Endocrine disorders, e.g. hyper-/hypothyroidism
• Blood pressure > 160/90 mmHg
• Severe cardiac function disturbances and severe heart rhythm disturbances
• Neoplasm
• Severe general diseases or mental disorders making the participation in the study
impossible
• Drug abuse
• Female patients during pregnancy and lactation period and female patients with active menses during the past year
• Hypersensitivity to benfotiamine or other constituents of the study medication
• HbA1c >9.5%
• Use of vitamin B containing supplements during the last 3 months
• Use of NSAIDs more than 3x per week (including self-medication)

• Participation in another study within one month before joining the benfotiamine
study

## Sample size calculation

The two primary outcome variables are quantitative. As primary outcome measure, the difference between the value at the end and the value at the start of medication is defined. It is assumed that the differences are normally distributed. P-values are adjusted for multiple testing by the Bonferroni-Holm-procedure. Hypotheses are one sided. As level of significance 2.5% are established.

It is proposed to have 38 evaluable patients per group. This sample size enables the study to detect an effect of size 0.65 with a power of 80%. Effect size is the difference in group means divided by the common standard deviation. For clarification: If (mean of the placebo group minus the mean of the verum group ) divided by the standard deviation is bigger or equal 0.65 then the study will deliver a significant result with a probability of at least 80%.

The drop-out rate is assumed to be 10%. Therefore 43 patients have to be randomised to each group to have 38 evaluable patients. For both groups together 86 patients are needed for admission to the study.

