## Confirmatory testing

Primary outcome variables are the differences of β2-microglobulin and albumin in 24 hour urine between end and start of study medication. Both primary outcome variables will be tested with the t-test for independent samples. In case the distribution of the variables is clearly not a normal distribution, then the t-test will be replaced by the Wilcoxon test. To solve the problem of multiple confirmatory testing the p-values of the two tests will be adjusted by the Bonferroni-Holm procedure. The level of significance is established as 2.5% for the one-sided hypotheses excretion with verum is less at the end of the medication phase than excretion with placebo.

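### The 80% power in section 4.4 leaves out the Bonferroni-Holm adjustment that the same section prescribes: power is about 71% if only one primary endpoint responds, and the claim does not say which power it means

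*Protocol*

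**What the plan says.** Section 4.4 (Sample size calculation) sets the frame in its first paragraph: "The two primary outcome variables are quantitative", "Hypotheses are one sided", "As level of significance 2.5% are established", and "P-values are adjusted for multiple testing by the Bonferroni-Holm-procedure". The next paragraph proposes 38 evaluable patients per group and states "This sample size enables the study to detect an effect of size 0.65 with a power of 80" per cent. Effect size is defined there as the difference in group means over the common standard deviation. A sentence of clarification adds that, if this ratio is 0.65 or more, "then the study will deliver a significant result with a probability of at least 80" per cent. With 10% drop-out the section arrives at 43 randomised per group, 86 in total.

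Section 9.2 (Confirmatory testing) fixes the same analysis: "Both primary outcome variables will be tested with the t-test for independent samples", and "the p-values of the two tests will be adjusted by the Bonferroni-Holm procedure".

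Section 4.4 does not say whether the 80% refers to a named endpoint, to at least one of the two, or to both. It does not say whether 0.65 is assumed for one endpoint or for each, and it gives no correlation between them. The objectives in the Summary and in section 2 name the two markers jointly.

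**The concern.** The power statement and the multiplicity rule stand in the same section but do not fit together. With two endpoints under Holm, the first rejection needs a one-sided p-value of at most 2.5%/2 = 1.25%, and the other endpoint is judged at 2.5% only after that. A power figure that describes this procedure has to include the stricter first step, and the stated 80% does not appear to.

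The justification for 86 patients rests on this sentence. An effect on one marker only is a realistic case here. Section 1 describes a glomerular component that leads to albuminuria and a tubulointerstitial component that largely follows from it, and expects benfotiamine to soften the effects of albuminuria on renal tissue. A change in the tubular marker without an equal change in albumin would fit that rationale. In that case the risk of missing a true effect of 0.65 is about 29%, not the 20% that a reader takes from section 4.4.

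**Working it through.** **Inputs from the protocol.** n = 38 evaluable per group, effect d = 0.65, one-sided level 2.5%, two endpoints with Holm (section 4.4); t-test for independent samples (section 9.2). **Assumption:** the correlation ρ between the two endpoints is not given, so a range is shown.

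**Formula.** For one t-test at one-sided level a, power = P(T > t₁₋ₐ,df), where T is noncentral t with df = 2n − 2 = 74 and noncentrality d·√(n/2) = 0.65 × √19 = 2.833.

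**Step 1: reproduce the plan's figure.** At a = 0.025 the critical value is 1.993 and power is 79.9%. The normal approximation gives Φ(2.833 − 1.960) = 80.9%, and its required sample size is exactly 38 per group (39 by exact t). The stated 80% with 38 per group is therefore the calculation for a single unadjusted test. The drop-out step is correct: 38/0.90 = 42.2, rounded up to 43.

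**Step 2: first Holm step.** At a = 0.0125 the critical value is 2.288 and power is 70.7%. The normal approximation gives Φ(2.833 − 2.241) = 72.3%.

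**Step 3: the full Holm procedure, both endpoints with d = 0.65.** Write p₁ = 0.707 (power at 1.25%) and p₂ = 0.799 (power at 2.5%). With independent endpoints:
- at least one rejection: 1 − (1 − p₁)² = 1 − 0.293² = 91.4%
- a given endpoint: p₁ + (p₂ − p₁)·p₁ = 0.707 + 0.092 × 0.707 = 77.2%
- both: 2p₁p₂ − p₁² = 1.129 − 0.499 = about 63%

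For correlated endpoints the procedure was simulated (200,000 replicates per scenario):

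| ρ (assumed) | Effect on one endpoint only: that endpoint | Effect on both: a given endpoint | Effect on both: both rejected | Effect on both: at least one rejected |
|---|---|---|---|---|
| 0 | 70.8% | 77.3% | 63.2% | 91.5% |
| 0.3 | 70.6% | 76.6% | 65.4% | 87.8% |
| 0.5 | 70.7% | 76.1% | 67.1% | 84.9% |
| 0.8 | 70.8% | 75.3% | 70.9% | 79.6% |
| 0.95 | 70.8% | 74.1% | 73.1% | 75.1% |
| 0.99 | 70.5% | 72.5% | 72.4% | 72.5% |

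**Step 4: what would match 80% at the first Holm step.** With 38 per group, the effect detectable with 80% power at 1.25% is 0.72 (0.7196). Holding the effect at 0.65 would take 47 evaluable per group (46 gives 79.7%, 47 gives 80.7%), or 47/0.90 = 52.2, rounded up to 53 randomised per group. This shows the size of the gap and is not a request for more patients.

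**The case against.** The strongest defence is that, with two Holm-tested endpoints, a significant result for the study can fairly mean at least one rejection. If 0.65 is the planning effect for both endpoints, power on that reading is 91% when they are uncorrelated and about 80% at a correlation of 0.8, so the claim is met or very nearly met. This stands as a possible reading. It does not settle the matter, because section 4.4 does not define success as at least one rejection, does not say that 0.65 must hold for both markers, and gives no correlation. The stated figures also coincide with the single-test calculation, which an at-least-one calculation would match only near a correlation of 0.8.

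A second defence is that section 7.5 has drop-outs replaced until the planned number is reached. If that means 43 completers per group, power at 1.25% is 76.6% (noncentrality 0.65 × √21.5 = 3.014, df 84). Section 7.5 can be read otherwise, and the result is still below 80%, so this narrows the gap without closing it.

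In the other direction, a reader might infer that the trial simply has 71% power, or is underpowered on every reading. The documents do not support that. The 71% belongs to the case in which only one endpoint responds. Nor do they support reading the jointly named objectives as a rule that both tests must succeed, since Holm lets either endpoint be claimed alone.

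**Conclusion.** The point holds in a conditional form. The 80% in section 4.4 was evidently computed without the adjustment that sections 4.4 and 9.2 prescribe, and its target is undefined. For a single responding endpoint the shortfall is about 9 percentage points (79.9% against 70.7%), whatever the correlation. With an effect of 0.65 on both endpoints, neither the power for a given endpoint nor that for both reaches 80% at any correlation tried. Only the power for at least one rejection does, up to a correlation of about 0.8.

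These figures rest on normally distributed changes, exactly 38 evaluable per group and assumed correlations. It might also be inferred that a baseline-adjusted analysis would win back most of the loss. That depends on the correlation between baseline and end values, which the protocol does not give, so it cannot be claimed.

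The matter should be fixed but does not threaten the design: the test, the level and the control of type I error are untouched.

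**What to change.** Keep 38 evaluable per group and restate section 4.4:
- Give the power as about 71% for an effect of 0.65 on a single responding endpoint at the first Holm step (one-sided 1.25%), or equivalently 80% for an effect of 0.72.
- The sponsor should state whether the claimed power refers to a given endpoint, at least one or both; for which endpoints the 0.65 is assumed; and, where both enter, the assumed correlation and the resulting power. The choice is the sponsor's and should agree with the objectives in the Summary and section 2.
- Bring the sentence of clarification about the probability of a significant result into line with that choice.

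The cost is protocol wording only, with no change to sample size, test or level. The drawback is that the stated power looks less favourable.

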# TREATMENT OF SUBJECTS

## Investigational product/treatment

Benfotiamine is the investigational treatment in this clinical trial. The medicinal product benfotiamine is a lipid-soluble derivative of thiamine (vitamin B1). The effect of this treatment will be compared to placebo in the study population.

## Use of co-intervention

During the run-in phase, treatment of the patients will be optimized in order to keep it mostly constant during the study period. Special attention has to be payed for following concomitant treatments which must not be changed during study:

- ACE inhibitors / RAS blockers
- Acetylic salicylic acid / NSAIDs
- Metformin
- Statins

If one of these medications has to be changed substantially during the study, the patient can continue the study or has to be withdrawn. In case of continuation of the study, the changes of medication have to be documented thoroughly.

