### Specific criteria for withdrawal

- Serious adverse events
- Hospitalization of the patient
- Non compliance of the patient
- Change of concomitant medication which might influence the primary and secondary endpoints itself (e.g. ACE-inhibitors, AT II-antagonists)

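### The co-medication rules conflict on whether a patient whose ACE inhibitor or similar drug changes after randomisation stays in the trial, so a partly discretionary decision determines whose week-12 primary outcome exists

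*Protocol*

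**What the plan says.** **After randomisation.** Section 5.2 (Use of co-intervention) names four groups, ACE inhibitors/RAS blockers, ASA/NSAIDs, metformin and statins, as "following concomitant treatments which must not be changed during study". If a substantial change is nevertheless needed, "the patient can continue the study or has to be withdrawn"; for those who continue, the change must be documented. Section 7.4.1 lists among its specific withdrawal criteria "Change of concomitant medication which might influence the primary and secondary endpoints itself", with ACE inhibitors and AT II-antagonists as examples, and mentions no continuation.

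**After withdrawal.** Section 7.5 admits further patients until the planned number is reached. Section 7.6 follows withdrawn patients through the clinic's ordinary diabetes care and pursues side effects. It does not ask for the week-12 24-hour urine.

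**Before randomisation.** Section 4.2 requires ACEi and/or AIIA "in an unchanged dose for at least 3 months", without saying from which date the 3 months are counted. Section 5.2 states: "During the run-in phase, treatment of the patients will be optimized in order to keep it mostly constant during the study period". It makes no explicit exception for ACEi/AIIA. The run-in lasts 6 weeks, and its check of microalbuminuria consists of "doing a 24 hour-urine analysis on two different occasions with 2-6 weeks in between". Section 4.2 asks for microalbuminuria "in at least two samples within 2-6 weeks in advance of inclusion in the trial".

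**Primary outcome.** Sections 4.4 and 9.2 define it as the difference between the end and the start of study medication, for β2-microglobulin and albumin in 24-hour urine.

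**The concern.** Two investigators could both follow the protocol and treat the same event differently. One keeps a patient whose ACE inhibitor is changed at week 6 and obtains the week-12 urine. The other withdraws the patient, obtains no urine and enrols a replacement. The choice comes after randomisation and may depend on how blood pressure, albuminuria or renal function are developing, which treatment could influence. The patients who reach week 12 are then no longer simply those who were randomised.

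An analysis plan written later cannot repair this, because urine that was never collected cannot be analysed. Replacement restores the count but not the comparability of the arms.

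The run-in wording is a lesser matter. The Introduction describes ACEi and AIIA as the mainstay of lowering albuminuria, and albumin is one of the two primary outcomes. A dose changed shortly before week 0 could leave albumin still moving when the baseline is taken.

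**Working it through.** **1. The plan's own figures reproduce.** Inputs from 4.4: effect size 0.65 SD, one-sided 2.5%, power 80%, drop-out 10%. The two-sample formula gives 38 per group (exact noncentral t power 79.9%). Then 38/(1 − 0.10) = 42.2, rounded up to 43 per group, 86 in total. The sample size is not in dispute.

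**2. One event, two outcomes.** Take a substantial change of ACE inhibitor dose after week 0:

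| Section | Consequence |
|---|---|
| 5.2 | Continue or be withdrawn; no criterion |
| 7.4.1 | Listed withdrawal criterion; no continuation |
| 7.5 | If withdrawn: replaced |
| 7.6 | If withdrawn: ordinary care; no week-12 urine required |

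For ACEi/AIIA, 5.2 and 7.4.1 disagree. For ASA/NSAIDs, metformin and statins, the investigator must judge whether the change could affect an endpoint.

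**3. What selection does to the estimate.** Let a share w of an arm be removed, with mean change e had they been measured, and let those retained have mean r. The full-arm mean is m = (1 − w)r + w·e, so r − m = w(r − e). The bias in the group difference is the difference of this term between arms. It is zero if w and (r − e) are the same in both. If w is 10% in one arm and 0 in the other, the bias is one tenth of the gap r − e; at 20% it is one fifth. The sign can go either way: losing worsening patients from placebo hides an effect, and losing them from verum exaggerates one.

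**4. Precision, for illustration.** The protocol gives no rate of co-medication change, so the shares below are assumptions. They are losses on top of the 10% drop-out, without replacement, from 43 randomised per group. Power is exact t for one endpoint at one-sided 2.5%, as in the plan's calculation.

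| Extra loss | Left per group, 43 × (0.90 − loss) | Power |
|---|---|---|
| 0% | 38.7 | 80.6% |
| 5% | 36.6 | 78.3% |
| 10% | 34.4 | 75.7% |
| 15% | 32.3 | 72.9% |
| 20% | 30.1 | 69.8% |

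If such patients stay in and the SD of change rises by 5, 10 or 20% (assumed), power at 38 per group is 75.9, 72.0 or 64.4%. These rises are demanding. If 10% of patients change medication and group means are unaffected, a 5% rise in overall SD needs a variance of (1.05² − 0.90)/0.10 = 2.0 times the usual in those patients; a 10% rise needs (1.10² − 0.90)/0.10 = 3.1 times.

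**5. Run-in timing.** Six weeks are 42 days; 3 months are about 91 days.
- Anchor at the end of the run-in, as the wording on qualifying samples suggests: an ACEi/AIIA dose changed in the run-in cannot have been unchanged for 91 days. The patient is ineligible, and the instruction to optimise collides with the criterion for these drugs.
- Anchor at screening: both rules can be met, but the dose is at most 42 days old at week 0, and the first qualifying sample may predate the change.

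**The case against.** The strongest reply on the main point is that 5.2 and 7.4.1 can be read together: withdraw when the change could influence an endpoint, otherwise continue with documentation. Part of this stands, since 7.4.1 does offer a criterion. But 5.2 does not refer to it, and for ACEi/AIIA the open choice in 5.2 remains against it. Under either reading, withdrawal still ends outcome collection.

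A second reply is that decisions are made blind. This limits deliberate steering, but not selection that follows treatment response.

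Several stronger readings are tempting and are not supported:
- A reader might infer that the baseline is undefined. It is defined as the value at the start of medication, with a week-0 visit in section 3. Only the stability of background treatment at that point is not secured.
- A reader might infer that the analysed patients are undefined. Analysis sets may be defined in an analysis plan that is not shown; the finding is confined to the conflicting retention rules and the uncollected urine.
- A reader might infer that everyone optimised in the run-in breaches the 3-month rule. That rule covers ACEi/AIIA only; adjusting metformin, a statin or ASA does not breach it.
- A reader might infer a certain contradiction between 4.2 and 5.2. This depends on the unstated anchor date. Moreover, the run-in is described as a phase of the study, so the ban on changing the listed drugs can be read as shielding them from optimisation.
- A reader might infer that run-in changes bias the comparison. They precede randomisation and mainly add noise.

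**Conclusion.** The point holds for post-randomisation handling. Sections 5.2 and 7.4.1 give different consequences for the same event. Together with 7.5 and 7.6, they let a partly discretionary decision remove a randomised patient's primary outcome and substitute another patient. The bias equals the difference between arms in (share removed × gap between retained and removed patients). Neither factor can be read from the protocol, so its size and direction are unknown. The power figures are illustrations on assumed shares, and replacement would offset the loss of numbers, though not the selection.

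The run-in point holds as a secondary ambiguity: no anchor date, and no explicit exception for ACEi/AIIA when treatment is optimised. Its likely consequence is extra variance in the change in albumin. The share of patients affected is not known.

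This deserves correction but does not invalidate the design. Which clinical rule should apply is not judged here.

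**What to change.** 1. Reconcile 5.2 with 7.4.1, and 4.2 with 5.2, into one consistent rule: which drugs may change, when, and what follows. The sponsor decides the clinical content.
2. State the date from which the 3 months of unchanged ACEi/AIIA are counted. Take both qualifying urine samples and the week-0 baseline under the same stability condition.
3. Separate stopping study treatment from leaving the study. Whatever is decided about study treatment, collect the week-12 24-hour urine of every randomised patient whose co-medication changes, unless the patient declines. Record the drug, date and reason for the change.
4. Include these patients in the primary analysis in the arm to which they were randomised. A sensitivity analysis may exclude them.

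The cost is protocol wording, a few extra urine collections and possibly a repeat qualifying sample for some patients. Retained patients may add slightly to the variance, and the estimate will then include the effect of co-medication changes. That is an acceptable price for keeping the randomised comparison intact.
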